In summary, while recent pioneering studies have begun to explore the longitudinal changes in the vaginal microecology of breast cancer patients undergoing endocrine therapy (23, 24), key knowledge gaps persist regarding the comparative effects of OFS + AI versus OFS + TAM on vaginal microbiota dynamics and the dose–response relationships between microbiome shifts and GSM severity. Therefore, this prospective cohort study aims to further contribute to this growing body of evidence by evaluating the effect of endocrine therapy on vaginal microbiome and GSM. This prospective cohort study aims to: (1) characterize the temporal changes in vaginal microbiome *α*-diversity (Simpson index), *β*-diversity, and relative abundance of predominant taxa (particularly Lactobacillus species) over 12 months in patients receiving endocrine therapy with ovarian function suppression; (2) compare the impact of two common regimens-ovarian function suppression combined with aromatase inhibitors (OFS + AI) versus ovarian function suppression combined with tamoxifen (OFS + TAM)-on vaginal microbiome composition; and (3) explore the associations between these microbiome changes and the severity of GSM symptoms, including potential dose–response relationships, as assessed by validated clinical measures (Vaginal Health Index, visual analog scales, and urinary symptom scores).

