### Cohort classification

This study employed an observational prospective cohort design with non-randomized grouping based on real-world clinical practice. Patients were categorized into two groups according to the endocrine therapy regimen prescribed by their treating clinicians, taking into account individual disease characteristics, age, prior treatment history, and personalized clinical needs. The prescription of OFS + AI versus OFS + TAM is determined by the treating oncologist in accordance NCCN (3) based on clinicopathological risk factors. In brief: (1) OFS + AI is preferred for patients at high risk of recurrenceor those with contraindications to tamoxifen; (2) OFS + TAM is considered for patients with intermediate risk or those who cannot tolerate AI; (3) Patient preference and comorbidities (e.g., baseline cardiovascular risk, endometrial abnormalities) are taken into account. Any patient using oral contraceptives or levonorgestrel-releasing IUDs is required to discontinue/remove them prior to enrollment, since hormone receptor-positive breast cancer is a contraindication for systemic or local hormonal contraceptives.

To assess and address potential confounding, comprehensive baseline data were collected, including demographic characteristics (age, BMI, educational level, marital status), clinicopathological features (tumor size, lymph node status, TNM stage, histological grade), immunohistochemical markers (ER, PR, HER2 expression status, Ki-67 index), treatment-related factors (surgical approach, chemotherapy history, radiotherapy history), and laboratory parameters (estrogen levels). Patients who received (neo) adjuvant chemotherapy are eligible for inclusion. By strictly enforcing the hormonal inclusion criteria (FSH < 40 IU/L and Estradiol >20 pg./mL), we ensure that even patients with prior chemotherapy exposure are in a biochemically confirmed premenopausal state at baseline. For these patients, baseline sampling and assessment are performed at least 4 weeks after the last chemotherapy dose and prior to the initiation of endocrinotherapy. Chemotherapy history (regimen, number of cycles, dates) is recorded as a potential confounder, and subgroup analyses stratified by chemotherapy exposure will be performed.

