A propensity score for receiving OFS + AI versus OFS + TAM will be estimated using a multivariable logistic regression model incorporating key baseline covariates, including age, BMI, tumor stage, prior chemotherapy exposure, and baseline ovarian function. Inverse Probability of Treatment Weighting (IPTW) will be used as the primary approach to balance baseline characteristics between the two groups. Stabilized weights will be calculated, which are truncated at the 1st and 99th percentiles to mitigate the influence of extreme weights. Standardized mean differences (SMD) will be assessed to confirm covariate balance, with an SMD < 0.1 considered acceptable.

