### Diversity analysis and community structure assessment

Alpha diversity was evaluated by calculating the Shannon Index and Simpson index based on the ASV abundance matrix to assess species richness and evenness within samples. Differences between groups were analyzed using the Kruskal-Wallis test. Beta diversity was assessed by calculating Bray-Curtis distances and weighted/unweighted UniFrac distances between samples and visualized using Principal Coordinates Analysis (PCoA). Permutational multivariate analysis of variance (PERMANOVA), implemented via the adonis function in the R vegan package, was used to quantitatively evaluate the variation in microbial community structure explained by clinical grouping. To ensure robustness, ASV-level analyses were compared with genus-level aggregated data as a sensitivity analysis.

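### The beta-diversity comparison is a PERMANOVA described by clinical grouping alone, and the article does not say how weighting, matching or covariates reach it, so as written its regimen result is open to confounding by indication

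*Protocol article*

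**What the plan says.** **The aim.** The Introduction lists, as its second aim, a comparison of OFS + AI with OFS + TAM in their impact "on vaginal microbiome composition".

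**The test.** Under Diversity analysis and community structure assessment, "Beta diversity was assessed by calculating Bray-Curtis distances and weighted/unweighted UniFrac distances between samples", and PERMANOVA through the adonis function "was used to quantitatively evaluate the variation in microbial community structure explained by clinical grouping". The one robustness check in that section is that "ASV-level analyses were compared with genus-level aggregated data as a sensitivity analysis".

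**Allocation.** Under Cohort classification: "This study employed an observational prospective cohort design with non-randomized grouping based on real-world clinical practice". Further, "Patients were categorized into two groups according to the endocrine therapy regimen prescribed by their treating clinicians", with disease characteristics, age and prior treatment among the considerations. OFS + AI is preferred at high recurrence risk, whereas "OFS + TAM is considered for patients with intermediate risk or those who cannot tolerate AI". The section itself names chemotherapy history as a potential confounder.

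**Confounding control.** Cohort classification states that "Inverse Probability of Treatment Weighting (IPTW) will be used as the primary approach to balance baseline characteristics between the two groups". The propensity model uses age, BMI, tumour stage, prior chemotherapy and baseline ovarian function. Statistical analysis adds propensity score matching for comparative analyses if a key covariate has a standardised mean difference (SMD) above 0.1. It also plans linear and generalised linear mixed models, and covariate-adjusted linear regression and mixed-effects models.

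**The concern.** PERMANOVA attributes to a grouping factor all the between-sample distance that lines up with that factor. If the women given OFS + AI have more often had chemotherapy, are at higher stage or differ in age, any effect of those factors on the vaginal community is credited to regimen unless the analysis removes it.

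The article recognises this threat and sets up a strategy against it. The strategy is not visibly connected to the one test that addresses whole-community composition. A significant result could then be reported as a regimen effect when it partly or wholly reflects who was prescribed what. If the regression and mixed-model results are adjusted while this one is crude, the two sets of results would answer different questions.

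Using one swab per woman at each visit does not cure this, because the bias comes from allocation and not from repeated sampling.

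**Working it through.** The article gives no figure for the PERMANOVA, so there is none to reproduce. The check has two parts.

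**1. Does any stated adjustment reach the test?**

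- *Diversity analysis section:* grouping is the only explanatory factor named. The sensitivity analysis concerns taxonomic level, not confounding.
- *Weighting (Cohort classification):* stated generally. It names no outcome analysis as included or excluded. Weights do not enter a standard PERMANOVA automatically, so a weighted version would have to be specified.
- *Matching (Statistical analysis):* triggered by SMD above 0.1 and intended for comparative analyses. On its wording it could cover this test, but it does not say so.
- *Covariate-adjusted models (Statistical analysis):* linear regression and mixed-effects models. Neither takes a distance matrix as outcome.

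A reader therefore cannot tell whether the PERMANOVA will be weighted, matched or crude. Taken on its own, the section describing it reads as crude.

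**2. How much could it matter?** The documents give no confounder prevalence or strength, so these are assumptions.

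*Inputs.* From the article: 55 women per group, Bray-Curtis distance, two-sided alpha 0.05. Assumed:

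- one visit with one swab per woman, one binary confounder, and no regimen effect
- eight-taxon Dirichlet communities with parameters 0.25 × (8, 1, 0.6, 0.4, 0.4, 0.3, 0.3, 0.2), the first taxon standing for Lactobacillus
- in exposed women, the first parameter multiplied by (1 − s) and the others by (1 + s), with s = 0.3 or 0.6
- 200 runs of 199 permutations per scenario

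*Mean Lactobacillus share implied.*

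- Unexposed: 8 / 11.2 = 0.71
- Exposed, s = 0.3: 5.6 / (5.6 + 3.2 × 1.3) = 5.6 / 9.76 = 0.57
- Exposed, s = 0.6: 3.2 / (3.2 + 3.2 × 1.6) = 3.2 / 8.32 = 0.38

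The confounder then explains about 4% (s = 0.3) or 13% (s = 0.6) of composition.

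*Imbalance.* SMD = (p1 − p0) / √{[p1(1 − p1) + p0(1 − p0)] / 2}. For 65% against 35%: 0.30 / √0.2275 = 0.63. For 75% against 25%: 0.50 / √0.1875 = 1.15.

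*Rejection rate for regimen at nominal 0.05.*

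| Confounder prevalence | SMD | About 4%: group only | About 4%: adjusted | About 13%: group only | About 13%: adjusted |
|---|---|---|---|---|---|
| 50% vs 50% | 0.00 | 0.050 | 0.040 | 0.075 | 0.065 |
| 55% vs 45% | 0.20 | 0.040 | 0.040 | 0.105 | 0.070 |
| 65% vs 35% | 0.63 | 0.130 | 0.045 | 0.395 | 0.030 |
| 75% vs 25% | 1.15 | 0.285 | 0.055 | 0.775 | 0.035 |

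The Monte Carlo standard error is √(0.05 × 0.95 / 200) = 0.015 near 0.05, and at most √(0.5 × 0.5 / 200) = 0.035.

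*Second set of assumptions.* Here chemotherapy lowers the mean Lactobacillus share from 0.70 to 0.60, 0.50 or 0.40, with 400 runs per scenario. Group-only rejection was 9%, 19% and 33% for chemotherapy in 70% against 40% of women. It was 13%, 39% and 66% for 80% against 30%. Entering chemotherapy before regimen gave 3% to 7% throughout.

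Both sets agree. The inflation grows with imbalance and confounder strength, and disappears once the confounder is in the model.

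**The case against.** The strongest reply is that the plan does provide for balance. Weighting is called the primary approach and excludes no outcome. Matching is triggered at SMD above 0.1 and lists chemotherapy history among its variables. A matched subset needs no change to PERMANOVA, since the distances are simply computed on the matched women. The larger simulated imbalances (SMD 0.63 and above) exceed the trigger several-fold, so matching would be activated in them. This stands in part. A reader might infer that the test has been placed outside the weighting plan, and the text does not support that. The link is unstated, not denied.

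Three further points have weight:

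- Analyses stratified by chemotherapy are planned, and could help expose a regimen signal that comes only from unequal chemotherapy.
- Eligibility requires premenopausal hormone levels and no antibiotics for 3 months, and baseline sampling is at least 4 weeks after chemotherapy. Both may limit carry-over.
- The abstract's primary outcomes are the Simpson index and Lactobacillus abundance, and mixed models also address individual taxa.

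Finally, a condensed article may leave the adonis formula to a fuller document. The article gives no formula, so the claim that grouping is the only term in the model would go too far. *Clinical grouping* is also not expressly defined as regimen, although with two regimen groups that is the natural reading.

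These points limit the claim but do not remove it. The article details propensity covariates, stabilised weights, truncation percentiles and an SMD threshold, yet describes this comparison by group alone. With weighting and matching both on offer, it leaves open which, if either, applies.

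**Conclusion.** The concern holds in this form: the only beta-diversity comparison is described by group alone, allocation follows prognosis and treatment history, and no section carries weights, matching or covariates into the test. Run as described, its R-squared and p-value for regimen are open to confounding by indication.

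The size is conditional. Across the tabulated scenarios, group-only rejection ran from 4% to 78% against a nominal 5%, with no visible inflation when confounding was weak and imbalance small. Adjusted rejection stayed between 3% and 7%. A reader might take the upper figures as this plan's false-positive rate. They are not, because they rest on assumed prevalence and strength and on neither weighting nor matching being used.

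The sponsor should settle this before results are seen, so that crude and adjusted versions are not chosen between afterwards. It concerns a stated aim, though not the primary outcomes as the abstract defines them.

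**What to change.** In the section on diversity analysis and community structure, state one of the following for the regimen PERMANOVA at each visit:

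- it includes the covariates already listed for the propensity score (age, BMI, tumour stage, prior chemotherapy, baseline ovarian function), or the estimated propensity score itself, with regimen tested marginally after them (for example adonis2 with by = 'margin', because adonis tests terms in sequence); or
- it is run on the matched sample defined under Statistical analysis.

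Report the adjusted partial R-squared, or the matched-sample R-squared, as the regimen result. Label the crude R-squared as descriptive only.

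**Cost.** One sentence and no new data, since these covariates are already collected. Covariate adjustment uses about 5 of the 110 − 1 = 109 degrees of freedom, more if stage is entered in several categories. The regimen R-squared may be smaller. The matching option would also drop any women left unmatched.

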### Primary outcome

This study identified vaginal microbial diversity and the relative abundance of Lactobacillus as the primary outcome measures. High-throughput sequencing of the 16S rRNA V3-V4 region was utilized, and bioinformatics analysis was conducted using the DADA2 pipeline via QIIME 2 to generate ASVs, enabling single-nucleotide resolution for quantitative assessment of alterations in vaginal microecological diversity. Species-level identification, particularly for Lactobacillus species, will be performed based on ASV taxonomic assignment. Simultaneously, the relative abundance of the Lactobacillus genus within the total bacterial community was analyzed to evaluate vaginal microecological homeostasis. Measurement time points were established at baseline, and at 1 month, 3 months, 6 months, and 12 months post-treatment, thereby creating a comprehensive longitudinal observation trajectory.

The collection of vaginal microbial samples followed a strictly standardized procedure: participants were instructed to abstain from sexual intercourse, vaginal medications, and douching for 48 h prior to sampling. Additionally, individuals who were menstruating were scheduled for sampling within a 3- to 7-day window following the cessation of menstruation to minimize interference from the menstrual cycle. During the sampling process, participants were positioned in the lithotomy position, and the cervix was fully exposed using a sterile vaginal speculum. A sterile cotton swab was rotated in the posterior vaginal fornix for a duration of 10 s, subsequently placed into a sterile tube containing DNA/RNA Shield preservative, temporarily stored at 4 °C, and then transferred to a – 80 °C ultra-low temperature freezer for long-term storage within 4 hours.

### Secondary outcomes

Prior to inclusion (at baseline), all patients undergo a systematic evaluation of GSM symptoms using standardized questionnaires, and only patients who report no GSM symptoms are eligible for inclusion. The clinical functional indicators comprised the Vaginal Health Index (VHI), Visual Analog Scale (VAS) scores for GSM, and International Consultation on Incontinence Questionnaire (ICIQ) scores for urinary symptoms. The VHI evaluated five dimensions through gynecological examination: vaginal discharge, pH value, epithelial integrity, moisture, and elasticity, with a cumulative score ranging from 5 to 25 points. Two attending gynecologists from our core multidisciplinary research team, each with over 10 years of clinical experience specializing in gynecological oncology and reproductive endocrinology, independently assessed the scores after undergoing protocol-specific standardized training to minimize inter-observer variability. The scores were then averaged, with measurements taken at time points baseline, 3 months, 6 months, and 12 months. GSM symptoms were assessed using a 10-cm VAS to independently evaluate subjective symptoms such as vaginal dryness, dyspareunia, and burning sensation, with scores ranging from 0 to 10 (0 indicating no symptoms and 10 indicating the most severe symptoms), completed by patients at each time point from baseline to 12 months. Urinary symptoms were evaluated using the International Consultation on Incontinence Questionnaire-Short Form (ICIQ-SF), with scores ranging from 0 to 21 points, measured at baseline, 3 months, 6 months, and 12 months, to encompass the full spectrum of genitourinary syndrome manifestations. Patients independently completed symptom questionnaires under the on-site guidance of research assistants, and comprehensive documentation of medication adherence, lifestyle changes, and other relevant factors potentially influencing vaginal microecology was maintained at each follow-up visit. The results are systematically documented in the electronic Case Report Form for all participants.

Routine monitoring encompassed a comprehensive evaluation of complete blood count, hepatic and renal function, lipid profile, and blood glucose levels, with intensified surveillance during the initial treatment phase—specifically at baseline and 1 month—to identify adverse drug reactions. Subsequent assessments were conducted at six-month intervals. The evaluation of hormone levels was pivotal in assessing the efficacy of endocrine therapy, involving the measurement of serum estradiol, follicle-stimulating hormone, luteinizing hormone, and testosterone using standardized electrochemiluminescence immunoassays (ECLIA) at baseline, 3 months post-treatment, and every 6 months thereafter to monitor the extent and persistence of ovarian function suppression (Table 1). Exploratory analyses will examine correlations between post-OFS hormone levels and vaginal microbiome diversity as well as GSM symptom severity. The inclusion of inflammatory markers, such as C-reactive protein and interleukins, into the testing panel was considered based on advancements in research and preliminary findings.

**Table 1 tab1:** Schedule of data collection.

Assessment category	Specific indicators	Baseline	1 Month	3 Months	6 Months	12 Months
Basic information	Demographics, medical history, tumor characteristics	✓	–	–	–	–
Treatment information	Endocrine therapy regimen, dosage, compliance	✓	✓	✓	✓	✓
Clinical examination	Vital signs, general condition	✓	✓	✓	✓	✓
Gynecological examination	Gynecological physical examination	✓	–	✓	✓	✓
	Vaginal health index (VHI)	✓	–	✓	✓	✓
	Urinary symptoms (ICIQ score)	✓	–	✓	✓	✓
Primary endpoint	Vaginal secretion sample collection	✓	✓	✓	✓	✓
	Vaginal pH measurement	✓	–	✓	✓	✓
Blood tests	Complete blood count, liver and kidney function	✓	✓	–	✓	✓
	Hormone levels	✓	–	✓	–	✓
Questionnaire	GSM symptoms (VAS score)	✓	✓	✓	✓	✓
Safety	Adverse event recording	–	✓	✓	✓	✓

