The vaginal microecosystem is crucial for maintaining the health of the reproductive tract (9, 10). Previous studies have thoroughly elucidates the molecular mechanisms and therapeutic strategies related to the female vaginal microbiome (10, 11). Estrogen deficiency leads to atrophy of the vaginal epithelium and depletion of glycogen, which compromises the survival of Lactobacillus species and results in dysbiosis, increased pH, and exacerbation of GSM symptoms (12, 13). Cross-sectional studies have shown that postmenopausal women exhibit increased vaginal microbial diversity with a significant reduction in Lactobacillus, which strongly correlates with GSM symptoms (14, 15). A multicenter analysis conducted in 2024 demonstrated that non-Lactobacillus-dominant microbial states, such as the enrichment of Gram-negative bacteria, significantly increase the risk of GSM development, further confirming that vaginal dysbiosis is an independent risk factor for GSM (16). Consequently, changes in the vaginal microbiome represent a crucial aspect of the pathophysiology of GSM. The depletion of Lactobacillus species and the proliferation of anaerobic bacteria are not only indicative of the GSM vaginal microenvironment but may also directly induce symptoms via inflammatory and metabolic pathways (15–20). Profiling the vaginal microbiome shows potential as a biomarker for assessing GSM risk, which could inform predictive, preventive, and precision intervention strategies in the management of GSM.

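### Aim 3 relates Lactobacillus and diversity to a Vaginal Health Index that includes vaginal pH, so a VHI association can arise or be inflated through that one item

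*Protocol article*

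**What the plan says.** The aims at the end of the Introduction include one to "explore the associations between these microbiome changes and the severity of GSM symptoms, including potential dose–response relationships", with severity taken "as assessed by validated clinical measures (Vaginal Health Index, visual analog scales, and urinary symptom scores". The VHI is thus one of three named severity measures.

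The Primary outcome section supplies the microbiome side: "vaginal microbial diversity and the relative abundance of Lactobacillus as the primary outcome measures".

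The Secondary outcomes section defines the VHI by "vaginal discharge, pH value, epithelial integrity, moisture, and elasticity, with a cumulative score ranging from 5 to 25 points". It is scored at baseline and 3, 6 and 12 months by two gynaecologists, whose scores are averaged.

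The Introduction says that the process set off by estrogen deficiency "compromises the survival of Lactobacillus species and results in dysbiosis, increased pH, and exacerbation of GSM symptoms".

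Table 1 schedules "Vaginal pH measurement" as a separate line at the same four visits as the VHI. It stands in the primary-endpoint block beside the swab, although the Primary outcome section does not name pH.

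The Discussion presents the dose-response analysis as a distinguishing feature of the study. It also foresees a prediction model that combines sequencing data with the VHI and other clinical measures. Nowhere does the article describe a VHI without its pH item, an item-level analysis, or a caution about pH in this association.

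**The concern.** Three statements meet in one analysis: pH is an item of the VHI, pH rises when Lactobacillus is lost, and the VHI is set against Lactobacillus as a measure of severity. If Lactobacillus falls and pH rises, the VHI changes even when the four items describing tissue and secretions do not.

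What is at stake is the meaning of a positive result. The VHI is the only examination-based measure of the three, so a Lactobacillus-VHI gradient is the result most easily taken as a link between dysbiosis and clinical atrophy. If pH alone carries the gradient, it shows only what the Introduction already takes as known. A prediction model with total VHI as its target would have the same weakness: part of its apparent performance would be prediction of pH.

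**Working it through.** The article gives no figure to reproduce here and no item correlations, so the size can only be illustrated under assumptions.

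**From the document.** The VHI has five items with a total of 5 to 25. The target sample is 110 (Sample size section). The abstract's 10% attrition leaves 110 × 0.9 = 99. Tests are two-sided at 0.05 (Statistical analysis).

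**Assumed.** Each item is scored 1 to 5, which fits the total range and gives pH 4 of the 20 scorable points (20%). Items have equal variance and a common inter-item correlation ρ from 0 to 0.5. Lactobacillus correlates r with the pH item, in absolute value, from 0.3 to 0.7.

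**Case A: only pH is linked to Lactobacillus.** The sum of five unit-variance items has variance 5 + 20ρ, so

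corr(total VHI, Lactobacillus) = r / √(5 + 20ρ).

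The chance of p < 0.05 in one cross-sectional test uses Fisher's z, with mean atanh(corr) × √(n − 3) compared with ±1.96.

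| r | ρ | corr. with total VHI | P(p < 0.05), n = 110 | n = 99 |
|---|---|---|---|---|
| 0.3 | 0 | 0.13 | 29% | 26% |
| 0.3 | 0.3 | 0.09 | 16% | 14% |
| 0.3 | 0.5 | 0.08 | 13% | 12% |
| 0.5 | 0 | 0.22 | 65% | 61% |
| 0.5 | 0.3 | 0.15 | 35% | 32% |
| 0.5 | 0.5 | 0.13 | 27% | 25% |
| 0.7 | 0 | 0.31 | 92% | 89% |
| 0.7 | 0.3 | 0.21 | 60% | 56% |
| 0.7 | 0.5 | 0.18 | 47% | 43% |

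The extremes by hand are 0.3/√15 = 0.08 and 0.7/√5 = 0.31. All nine correlation structures are mathematically possible. In every one, the correlation with the four-item VHI is exactly 0.

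**Case B: the other four items are also linked, each with correlation g.**

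Total VHI: (4g + r) / √(5 + 20ρ). VHI without pH: 4g / √(4 + 12ρ).

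- g = 0.2, r = 0.5, ρ = 0.3: 1.3/√11 = 0.39 with pH; 0.8/√7.6 = 0.29 without.
- g = 0.2, r = 0.5, ρ = 0.5: 1.3/√15 = 0.34 with pH; 0.8/√10 = 0.25 without.
- g = 0.3, r = 0.3, ρ = 0.3: 1.5/√11 = 0.45 with pH; 1.2/√7.6 = 0.43 to 0.44 without.

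In the last line pH is no more strongly linked than any other item, and its removal hardly matters. The distortion is material when pH follows Lactobacillus more closely than the tissue items do.

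**The case against.** The strongest reply is that pH belongs to the condition. The VHI is named in the aims as a validated measure, and the Introduction has estrogen deficiency causing epithelial atrophy, Lactobacillus loss, higher pH and symptoms in one sequence. On that account Case A, with no link to any tissue item, is unlikely, and Case B is nearer the truth: a real association made larger, not a false one. This stands as a limit on size. It does not remove the problem, because a total that includes pH cannot tell the two cases apart.

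The reach is also limited. The aim is worded as exploratory. The VAS is used to "independently evaluate subjective symptoms such as vaginal dryness, dyspareunia, and burning sensation" and has no pH item, nor does the ICIQ-SF. A VHI signal without a VAS signal would be visible. The calculation treats one cross-sectional test, whereas the article plans longitudinal mixed models and Bonferroni correction where appropriate, so the percentages do not forecast the study's error rate.

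A reader might infer that predictor and outcome share a component. They do not: diversity and Lactobacillus abundance come from 16S sequencing and contain no pH. By the article's own account pH is a downstream marker that sits inside the outcome. A reader might also infer from Table 1 that pH is used as a microbiome variable. No described analysis does so, and the Primary outcome section leaves pH out; the row position is a labelling slip.

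Finally, a with-and-without check could sit in an unseen analysis plan. That is possible, but the article itself fixes the VHI, pH included, as a severity measure for this aim, and says nothing that limits how the result may be read.

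**Conclusion.** The point holds for the VHI part of aim 3 and for any prediction model that uses total VHI. As written, an association between the microbiome and total VHI can arise or be inflated through pH, so on its own it does not support a link to epithelium, moisture, elasticity or discharge.

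The size is unknown. Under the assumed ranges it runs from a correlation of about 0.08 to 0.31 if pH alone is linked (about 13% to 92% chance of p < 0.05 at n = 110, against a nominal 5%) to a moderate inflation, such as 0.39 against 0.29, if the other items are linked as well.

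The document does not support the stronger conclusion that the whole microbiome-GSM aim is circular, or that a VHI association would be spurious. Two of the three severity measures are untouched, and using the VHI is not an error in itself. Nor would removing pH make the association causal, since falling estrogen may drive both sides. This is a worthwhile, inexpensive improvement and not a flaw in the design.

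**What to change.** For aim 3 and any microbiota-GSM prediction model, state in advance that the VHI-microbiome association will be estimated twice with the same model: for the total VHI (5 to 25) and for the VHI without its pH item (4 to 20, if items are scored 1 to 5). Report pH as an outcome of its own. State that a link to clinical atrophy will be claimed only if the association holds without pH. Keep the total VHI for the OFS + AI versus OFS + TAM comparison.

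The cost is one extra analysis, on a subtotal that is not the published score and so lacks its validation; this is why the total stays alongside it. No new measurement is needed, since pH is already scheduled at every VHI visit. The article does not say whether item scores are kept or only totals, so the case report form should be confirmed to hold them.

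Separately, and minor: align the primary-endpoint label for vaginal pH in Table 1 with the Primary outcome section, which does not list pH.
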